### Randomization & study blinding

The study statistician will a priori randomize 400 study ID numbers to one of two arms in a 1:1 ratio. The list will be shared with the intervention coordinator. When a couple is enrolled, the intervention coordinator will consult this list and informs the nurse-counselors of the assignment using a password-protected online log. During the baseline visit, the husband will be shown how to use the breathalyzer by a male assessment team member and asked to blow into it every day for seven days. The following week, the assigned nurse-counselor will contact the couple to inform them of their assigned group and schedule the first session. Assessment team members will be blinded to group assignment to minimize performance bias.

Following the final 12-month follow-up assessment, control arm couples will be offered four sessions of the intervention, if interested. After intervention completion, the study statistician will randomly select couples stratified by complete vs. incomplete intervention attendance to participate in qualitative IDIs. Every two months, the study statistician will select approximately 20 percent of the number of couples available that round. This process balances random selection with ensuring couples can accurately recall their intervention experience. 

### Data collection

Data collection will take place in person at five timepoints: baseline (pre-intervention) and three-, six-, nine-, and 12-month follow-up. Study staff will solicit support from ASHAs, PHC medical officers, and community-based non-governmental organizations who work with women and are well-known to PHC staff. After informed consent, research staff will administer baseline questionnaires using REDCap on study tablets. The husband will receive a reminder via text message to use the breathalyzer every day and to send a photo using it the subsequent week. At all remaining quarterly follow-up outcome assessments, the seven-day breathalyzer assessment will precede questionnaire administration. Breathalyzers will be dropped off and collected by members of the assessment team.

To assess the hypothesized mediators and mechanisms of change, IDIs will be conducted with the qualitative subsample at two time points: within three months after the end of the intervention and upon completion of the 12-month follow-up. Spouses will be interviewed separately by trained qualitative interviewers, with interviews audio-recorded, transcribed in the local language (Kannada), and translated to English for analyses.

### Participant safety

One potential risk in IPV intervention research is an increase in IPV. No increases in IPV were noted in our pilot study in India. [37] The intervention approach entails presenting the intervention to participants as a communication- and relationship-enhancing intervention and not an IPV intervention directly. [102] This framing is used to increase intervention acceptability and reduce stigma related to IPV and participation in substance use programs and mental health services. We will not include those with severe alcohol dependence or severe IPV because the intervention is not designed for those cases. All staff will be routinely trained in issues related to IPV and alcohol use and associated stigma as well as in safety procedures to enable them to respond to circumstances of distress. To address potential risks, we will refer participants who experience exacerbation in violence to local, integrated services with whom we have close contact. At any point in the study, if an enrolled wife expresses a desire for further support for the violence, we will refer her to legal and/or integrated support organizations, a few of which are headed by members of Harmony’s Community Advisory Board. Participants will be assessed at each follow-up for clinically significant depressive symptoms and suicide risk and offered referrals to the psychiatrist or the nearest hospital for consultation and care in case of moderate or severe risk of suicide or harm to self (as assessed by the study clinical psychologist). The Data Safety & Monitoring Board will closely review safety data. Our Data and Safety Monitoring Plan (DSMP) includes a detailed plan to monitor and mitigate risk. A consultant with expertise in gender-related health issues conducts regular gender sensitization and safety workshops with the study staff and will be available to the team for ad-hoc consultations and support.

### Data analysis

#### Quantitative.

We will perform intention-to-treat (ITT) analyses to compare the treatment and control groups on the two primary outcomes: 1) mean overall AUDIT score as the measure of alcohol use; and 2) mean overall IFVCS score as the measure of IPV. We hypothesize that the treatment group will show a lower mean AUDIT score and a lower mean IFVCS score than the control group participants at 12-month follow-up. We will analyze this via a linear regression model for each outcome, in which we will control for the baseline outcome score and any relevant covariates for which the treatment groups might differ at baseline, despite randomization. A multilevel version of the models will be used for the longitudinal analyses, with repeated measures nested within participants and a random intercept for participants. The treatment arm*wave interaction will serve as the test of the intervention effect. Since each of these outcomes will only be collected from one of the spouses (alcohol use from the male and IPV from the female),combining/controlling for multiple reports within the couple is not necessary. If despite our extensive, proven-effective retention efforts, there is a substantial amount of missing data, we will use multiple imputations, assuming data are missing at random, including socio-demographic and other variables as auxiliary variables as appropriate, to perform sensitivity analyses of the original results [103].

Secondary analyses will consist of similar ITT linear regressions as for IFVCS above for the secondary outcomes of mean CPQ and breathalyzer scores. We hypothesize that post-intervention, the treatment group will show more positive and less negative communication patterns than the control group. We also expect that intervention participants will have lower post-intervention breathalyzer scores, on average, than the control group, reflecting reductions in frequency and quantity of alcohol use. Like the primary outcomes, the breathalyzer data is only available from one spouse, but CPQ data will be collected from both spouses. CPQ subscale scores will be constructed based on each spouse’s report separately, and agreement assessed via intraclass correlations. The treatment effect will be explored using husband and wife reports as the outcome variable in separate models to allow a differential effect of the treatment on mean CPQ subscale scores as reported by each partner in the couple [104].

Mediation analyses will assess if the effect of the intervention on the primary outcomes (AUD and IPV) was mediated by change in the theorized drivers and intermediate variables (e.g. self-efficacy, anger management, coping skills), by assessing the effect of the intervention on the mediators and of both the mediators and the intervention on the outcome. This will be tested via structural equation models (SEM) with bootstrapped confidence intervals for the indirect effects [105]. SEM can also accommodate dyadic analyses in which variables reported by both spouses are included in the same model and estimate both ‘actor’ and ‘partner’ effects (e.g. effect of change in wife’s report of marital relationship on change in wife’s CPQ score and on change in husband’s CPQ score, respectively) [106]. We will also examine whether personality factors, such as impulsivity and gender norms, moderate the intervention effect. Moderation will be assessed by including an interaction between the potential moderators and the intervention variable in the regression model. Based on the global literature, including studies from India, [107–112] on impulsivity, gender equity attitudes, alcohol and IPV, we hypothesize that the intervention impact will be less among men who score highly on impulsivity and have lower score on gender equitable norms. Other secondary, preliminary analyses will rerun the ITT models above, but with intervention dose (number of sessions attended) added to the models.

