### Sample size determination

Sample size was determined based on the power necessary to detect a meaningful intervention effect at 12 months in the continuous primary outcomes. Based on our pilot results, [36] we expect the intervention group to have a 4-5 point lower mean IFVCS score compared to the control group at the end of the study (SD = 14). With alpha = 0.05, power = 80%, this requires an effective sample size of n = 320. Allowing for 20% attrition, the initial sample size necessary is 400 couples. This anticipated effect translates into a standardized minimum detectable effect size of d = 0.31, a small effect according to Cohen. [71] Since we will treat the AUDIT as continuous as well, we are similarly powered for a significant minimum detectable effect size of 0.31 standard deviations difference between the two groups on this second primary outcome. This is within our expectations based on a meta-analysis [72] that found a standardized mean difference of 0.29–0.38 with brief one-session interventions or usual care, respectively.

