#### Secondary.

Key secondary outcome measures include number of days (0–7) with a negative breathalyzer test over a one-week period prior to each follow-up interview and scores on the Communications Patterns Questionnaire (CPQ) [79] to assess couples’ communication and related behaviors during and after conflict interactions. A complete list of measures is included in Fig 1 and Table 2. All scales have been validated for use in India.

**Table 2 pone.0335332.t002:** Outcome variables, measures and intervention strategies.

Key Model Variables	Husband or Wife	Description of Scales	Intervention Strategies
**Demographics** *BL*	H, W	Age, years married, arranged marriage, children, living situation, education, religion, and income	
**Self-Efficacy** *BL, 6mo, 12mo*	H	Situational Confidence Questionnaire (SCQ) [80]: eight items assessing self-efficacy in resisting urge to drink heavily in alcohol-related situations	• Elicit participant-specific motivations, fears, and ambivalence and evoke change talk to facilitate behavior change (MI) • Collaboratively develop plan for change and problem-solve barriers (MI) • Provide coping skills to resist drinking urges (BCT)
**Motivation to Change** *BL, 6mo,12mo*	H	12-item Readiness to Change questionnaire for use in brief, opportunistic interventions among excessive drinkers [81]	
**Coping Skills** *BL, 6mo, 12mo*	H, W	Brief COPE [82]: a 28-item scale that assesses the use of different coping strategies for challenging situations	
**Alcohol Consumption and Dependence** *Primary and secondary outcome: quarterly*	H	Alcohol Use Disorders Identification Test (AUDIT) [78,83]:10 items measuring alcohol consumption, drinking behaviors and alcohol-related problems Number of negative breathalyzer tests in 7 consecutive days prior to quantitative interview	• Facilitate increased awareness of drinking patterns (MI) • Elicit negative consequences of alcohol use (MI) • Support reduced alcohol use (MI) • Develop daily trust contract for accountability to maintain sobriety (BCT) • Review positive reasons for sobriety, distracting activities and positive self-talk (BCT) • Identify interpersonal triggers and ways to avoid alcohol use (BCT)
**Alcohol Expectancies** *BL, 6mo, 12mo*	H	Alcohol Outcome Expectancies questionnaire: 38 items assessing positive and negative alcohol use expectancies [84,85]	
**Context of Drinking** *BL, 6mo, 12mo*	H	Five items measuring social and interpersonal contexts of alcohol consumption [86,87]	

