**Context of IPV** *BL, 6mo, 12mo*	H, W	14 items measuring social and interpersonal contexts of IPV [86–88]	• Promote positive relationship dynamics, provide safe discussion space to explore conflict, violence, and relationship impact (BCT)
**Attitudes Towards Violence** *BL*	H	Gender-Equitable Men (GEM) scale, IPV subscale: 4 items assessing attitudes towards gender norms in intimate relationships [10,89]	
**Intimate Partner Violence** *Primary Outcome: BL, 6mo, 12mo*	W	Indian Family Violence and Control Scale (IFVCS): 63 items to measuring control, psychological, physical, and sexual violence/coercion [40]	• Link violence to stressors and drinking patterns (BCT)
**Marital Relationship** *BL, 6mo, 12mo*	H, W	17 items assessing the frequency of positive interactions between spouses in the past month [36,90,91]	• Build skills to improve relationship dynamics (BCT)
**Communication Skills** *Secondary outcome:* *quarterly*	H, W	Communications Patterns Questionnaire (CPQ): 35 items assessing couple’s behavior patterns during and after conflict interactions [79]	• Teach active listening skills (BCT) • Promote healthy communication (BCT)
**Anger Management** *BL, 6mo, 12mo*	H	Clinical Anger Scale (CAS): 21 items assessing clinical anger and treatment progress [92]	• Promote emotion regulation through improved communication (BCT)
**Family and Financial Stress** *BL, 6mo, 12mo*	H, W	Chronic Strain Checklist (CSC): 23 items assessing family, marital, financial and work-related stressors [93,94]	• Identify life stressors and their relation to relationship problems and drinking patterns (MI, BCT)
**Decision Making Power** *BL, 6mo, 12mo*	H, W	Sexual Relationship Power Scale (SRPS): 9 items assessing decision-making power in the relationship [95] and three additional items on financial decisions	• Facilitate joint financial and general decision-making (BCT)
**Stigma** *BL, 6mo, 12mo*	H, W	• Alcohol-adapted Perceived Devaluation-Discrimination scale (PDD), adapted: 13 items assessing perceived alcohol stigma [96] • IPV Stigma Scale: 20 items assessing or internalized, anticipated, and perpetrator stigma, and isolation [97]	• Increase knowledge and identification of consequences of stigma related to alcohol use and interpersonal violence (BCT)

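### The random-intercept multilevel model can understate the standard error of the arm-by-wave test, mainly for AUDIT, unless all visits are equally correlated

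*Protocol article*

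**What the plan says.** The Quantitative part of Data analysis describes two analyses of the primary outcomes.

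- The hypothesis is "a lower mean AUDIT score and a lower mean IFVCS score than the control group participants at 12-month follow-up". For it the article says: "We will analyze this via a linear regression model for each outcome, in which we will control for the baseline outcome score". This has one record per participant.
- For the repeated measurements it says: "A multilevel version of the models will be used for the longitudinal analyses, with repeated measures nested within participants and a random intercept for participants". Directly after that it adds: "The treatment arm*wave interaction will serve as the test of the intervention effect".

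No random slope, residual correlation structure or robust standard error is named. It is not stated whether wave is linear or categorical, or whether baseline is an outcome row or a covariate in the multilevel version.

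On timing, Data collection says: "Data collection will take place in person at five timepoints: baseline (pre-intervention) and three-, six-, nine-, and 12-month follow-up". Table 2 labels the alcohol measures "Primary and secondary outcome: quarterly" and the violence measure "Primary Outcome: BL, 6mo, 12mo". AUDIT therefore has five waves and IFVCS three, or four and two follow-up waves if baseline is a covariate.

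**The concern.** With a random intercept as the only source of within-person correlation, months 9 and 12 are assumed to be no more alike than months 0 and 12. Every participant in an arm is also assumed to follow the same underlying slope apart from independent noise. The null tested is then that the arms do not differ and that individual courses are parallel.

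Arm by wave is a contrast of within-person change, and its variance is what this structure gets wrong when correlation decays or slopes vary. The model can then reject because participants drift differently, not because the arms differ.

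The article gives reasons to expect differing courses. It hypothesises that impulsivity and gender norms moderate the effect. It stops session scheduling at five months whatever the attendance, plans a dose analysis, and refers control husbands to outside treatment. At stake are intervals that are too narrow and p-values that are too small for the analysis named as the test of the intervention effect.

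**Working it through.** **The plan's own figure.** Sample size determination says: "With alpha = 0.05, power = 80%, this requires an effective sample size of n = 320". For d = 0.31, two-sided (assumed), n per arm = 2(1.96 + 0.842)²/0.31² ≈ 163.4, so 164 per arm or 328 in total, within 3% of 320. At 160 per arm the minimum detectable effect is 2.802 × √(2/160) = 0.313. Attrition: 320/0.8 = 400. The calculation is for a two-group difference in means at 12 months and uses no repeated-measures covariance.

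**Formula.** Let S be the true within-person covariance over T waves and c a contrast over waves that sums to zero. With balanced data the random-intercept model estimates the variance of c as c′c × w, where w = (trace S − sum S/T)/(T − 1). The true variance is c′Sc. With VR = c′Sc/(c′c × w), type I error = 2[1 − Φ(1.96/√VR)].

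**Worked example (assumed): AUDIT, five waves, unit variance, autoregressive correlation 0.7 per quarter.**
- Mean pairwise correlation = (4×0.7 + 3×0.49 + 2×0.343 + 0.2401)/10 = 0.520, so w = 0.480.
- Linear wave, c = (−2, −1, 0, 1, 2): c′c = 10 and c′Sc = 10 + 5.6 − 0.98 − 2.744 − 1.921 = 9.955. VR = 9.955/(10 × 0.480) = 2.07. The standard error is understated by a factor of 1.44 and type I error is 17.3%.
- Month 12 versus baseline: VR = (1 − 0.240)/0.480 = 1.58, factor 1.26, type I error 11.9%.
- Month-12 arm difference, baseline as covariate: residual variances at months 3 to 12 are 1 − 0.7²ᵏ for k = 1 to 4, i.e. 0.510, 0.760, 0.882 and 0.942, with mean 0.774. The model applies the mean to month 12. VR = 0.942/0.774 = 1.22, type I error 7.6%.

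**AUDIT, five waves, range of assumed patterns (type I error, %).** Random slopes use intercept variance 0.5, residual variance 0.5 and 12-month slope variance 0.2-2.0 times the residual variance. The mixture is stable 0.3 + decaying 0.5 + noise 0.2, with decay 0.5-0.8 per quarter.

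| True pattern | Linear arm × wave | Month 12 vs baseline | Joint 4-df test |
|---|---|---|---|
| Equal correlation | 5.0 | 5.0 | 5.0 |
| Random slopes | 6.1-13.4 | 5.8-11.2 | 5.0-5.8 |
| Mixture | 10.5-12.0 | 7.6-8.9 | about 5.6 |
| Autoregressive, 0.3-0.9 per quarter | 9.9-20.8 | 7.0-15.0 | 5.5-7.8 |

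With baseline as covariate (four waves), linear wave gives 8.7-16.0% (autoregressive) and 5.5-9.1% (random slopes). The month-12 arm difference from that model gives about 5-10%.

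**IFVCS.** With three waves and 0.7 per quarter, the correlations are 0.49, 0.49 and 0.240 (mean 0.407). VR = 0.760/0.593 = 1.28, type I error 8.3%; across the patterns with unequal correlation it is about 6-10%. With two follow-up waves and baseline as covariate there is only one pair of visits, so VR = 1 and the interaction test holds 5%.

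**Check by fitting the model.** A restricted maximum likelihood simulation (320 participants, five waves, linear wave, 250 runs each) gave 4.8% under equal correlation, 18.8% under autoregressive 0.7, and 9.2% under random slopes with variance 0.6 times the residual. The Monte Carlo standard error is about 1.4-2.5 points.

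**The case against.** The strongest reply is that the stated 12-month hypothesis has its own analysis, a baseline-adjusted regression with one record per participant. No within-person covariance enters it, and the trial is sized on the same comparison. That stands. A reader might infer that a null trial would be declared positive on AUDIT two to four times too often. The article does not support this for the 12-month regression; it could apply only if the multilevel interaction decided the result. The interaction still cannot be set aside as descriptive, because the article calls it the test of the intervention effect.

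A reader might also infer that the standard errors are too small as a matter of fact, or that 11-20% is the AUDIT error rate. Neither follows. The covariance is not given, and equal correlation produces no error. The upper range needs linear wave, all five waves as outcomes and strong serial decay, while the article leaves wave coding open. Its multilevel version of baseline-adjusted models can be read as keeping baseline as a covariate, which lowers the figures.

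Finally, this is a condensed article, and covariance details are often left to an analysis plan. It does not say that the random intercept is the only term, and it excludes neither serial correlation nor robust standard errors. That softens the point without removing it: a specific structure is stated and the test of effect is attached to it.

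**Conclusion.** The point holds in a conditional form. As written, the longitudinal arm-by-wave test is anti-conservative for a linear trend or a 12-month-versus-baseline contrast unless correlation is equal across visits and underlying slopes are common. AUDIT is the outcome chiefly exposed. Its type I error runs from 5% to about 21% across the assumed patterns, with about 6-13% for the milder ones. The joint categorical-wave test is little affected, and so is IFVCS, where the inflation vanishes for the interaction with two follow-up waves and baseline as covariate. All these figures assume complete, balanced data and correlation patterns that the article does not supply. The 12-month baseline-adjusted regression is sound on this point. Which of the two analyses governs the conclusion is a separate question, not settled here.

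**What to change.** In Data analysis, Quantitative, replace the random-intercept clause for AUDIT and IFVCS with: wave as a categorical factor and an unstructured within-participant covariance; if this does not converge, a random intercept and a random slope for time, with cluster-robust standard errors by participant. Take the longitudinal arm effects and their confidence intervals from that model.

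The cost is one sentence. An unstructured covariance has at most 5×6/2 = 15 parameters for AUDIT and 3×4/2 = 6 for IFVCS, which 320-400 couples support easily. Intervals become slightly wider where correlation is unequal, and almost nothing is lost if it is truly equal. Other adequate choices exist, such as a serial residual structure. What matters is that the covariance is not restricted to a random intercept.

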### Procedures

#### Intervention arm.

The Harmony intervention consists of 10, hour-long sessions delivered once weekly (Table 1) during a three- to five-month period. Initially, the husband receives three individual sessions of MI as well as one session jointly with his wife to address alcohol use, which is the standard primary care-based intervention to reduce AUD in community populations. The MI sessions focus on specific individual, interpersonal, and social factors driving disordered alcohol use by utilizing the four-step process of engaging, focusing, evoking and planning. [62] The intervention is presented to participants as a means of improving the couple’s communication and marital relationship (rather than explicitly as an AUD/IPV intervention) to reduce the potential stigma of attending sessions focused on AUD/IPV. The husband receives training in drink refusal, emotion regulation, problem-solving, and urge management skills. The nurse-counselor co-constructs a weekly change-and-action plan to help the husband use these skills between sessions. The nurse-counselor invites the wife to the fourth MI session, which orients the couple to lapse and relapse prevention and management. This joint session marks the transition to BCT. Following this, both spouses receive six sessions of BCT together [40] to improve interpersonal communication, caring, and trust.

**Table 1 pone.0335332.t001:** Summary of MI* + *BCT Intervention.

Session Number	Session Content	Session Participants
1-4	• Engaging, focusing, evoking and planning • Drink refusal, emotion regulation, problem solving, and urge management skills • Relapse prevention and management	Husband in 1–3 Husband and Wife in 4
5	• Trust: Daily Trust Contract	Husband and Wife
6	• Coping: Catching yourself, time-out, diaphragmatic breathing, relaxation, positive self-talk	Husband and Wife
7	• Effective communication • Joint problem-solving	Husband and Wife
8	• Caring: Catching your partner being nice and telling them	Husband and Wife
9	• Active listening • Expressing feelings directly using I-statements	Husband and Wife
10	• Review and wrap-up	Husband and Wife

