The first BCT session focuses on the development of a daily trust contract in which the husband verbally commits to reducing his drinking while his wife acknowledges her support and appreciation. The second BCT session discusses specific strategies to cope with stress and reduced alcohol use (including time-outs, a diaphragmatic breathing exercise, and engaging in positive self-talk). Effective communication and joint problem-solving are core components of session three, followed by mutually caring activities in BCT session 4. The fifth BCT session expands on effective communication by helping couples learn and practice active listening and using “I” statements to reciprocally express feelings in a direct manner. The last BCT session includes review and wrap-up, with couples revisiting useful topics and skills and planning for long-term improvement in alcohol use and relationship quality. All sessions include role plays and end with simple homework practice assignments. In addition, nurse-counselors use in-session charts with visuals and limited text, due to variability in participant literacy levels, to enhance participant comprehension and reinforce lessons and skills taught.

The intervention window is five months to allow for missed visits due to family holidays, illness, and travel. During their first visit, the couple is informed that session scheduling attempts will be discontinued after five months, regardless of the number of sessions attended at that point.

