#### Control arm.

Our prior work in India has shown a lack of availability of care for AUD and/or IPV in PHCs, as well as lack of adherence to existing protocols. [76,77] To meet ethical guidelines, the control arm participants receive a single session of enhanced usual care, consisting of (1) validation and safety planning for the wife; (2) referrals to provide medical-legal and shelter support; and (3) a brief educational intervention to the husband on alcohol use, based on the World Health Organization’s manual for managing AUD in primary care settings, [74] and a referral to tertiary care mental health (NIMHANS) and addictions treatment center. These will be carried out within two months of the baseline assessment by a trained nurse practitioner who is not involved in delivering the intervention.

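### Adding sessions attended to the 12-month ITT regression turns the arm term into an extrapolated zero-session contrast and the dose term into a confounded within-arm association

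*Protocol article*

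**What the plan says.** The last sentence on mediation, moderation and dose in the protocol article (Data analysis, Quantitative) labels the dose work as secondary and preliminary. The plan there is to "rerun the ITT models above, but with intervention dose (number of sessions attended) added to the models". The models it refers to are set out earlier in that section. The 12-month comparison is a linear regression of each outcome on arm, with this adjustment: "we will control for the baseline outcome score and any relevant covariates for which the treatment groups might differ at baseline, despite randomization". For the repeated measures, a mixed model with a random intercept is planned, and there "The treatment arm*wave interaction will serve as the test of the intervention effect".

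Three other places fix what dose means:

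- **Intervention arm:** "The Harmony intervention consists of 10, hour-long sessions delivered once weekly", so dose can run from 0 to 10. The couple is told that "session scheduling attempts will be discontinued after five months, regardless of the number of sessions attended at that point".
- **Control arm:** "the control arm participants receive a single session of enhanced usual care". Under Randomization & study blinding, control couples are offered intervention sessions only after the final 12-month assessment.
- **Randomization & study blinding:** incomplete attendance is expected, because the statistician will "randomly select couples stratified by complete vs. incomplete intervention attendance" for the interviews.

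**The concern.** Sessions attended is decided after randomisation and is constant in the control arm. Putting it beside arm in one regression changes the meaning of both coefficients. The arm term no longer compares the groups as randomised, so the rerun is not an ITT analysis. The dose term compares couples who attended more with couples who attended less. These may differ in motivation, drinking or violence in ways that the baseline score does not fully capture. The trial's own theory treats motivation and self-efficacy as drivers of change in drinking, so such a link is plausible, though its sign and size are unknown.

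At stake is how a reader would take the two coefficients. A non-zero arm term could look like harm or benefit where there is none. A near-zero arm term could look like no effect where there is one. The dose slope could look like a dose-response. Apparent harm matters in a trial that names increased violence as a risk.

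**Working it through.** **The plan's own figures.** Sample size determination gives SD 14, a 4 to 5 point difference, alpha 0.05, power 80%, effective N 320, 20% attrition, N 400 and d = 0.31. Taking alpha as two-sided:

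- n per arm = 2(1.960 + 0.842)²/0.31² = 163.3, so 164 per arm or 328 in all, close to 320.
- Detectable d at 160 per arm = 2.802 × √(2/160) = 0.313, or 0.313 × 14 = 4.4 points.
- 320/(1 − 0.20) = 400.

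These reproduce. The article gives no figure for the dose analysis, so the check below uses 160 per arm and SD 14.

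**Algebra.** With control dose fixed at 0, only intervention couples inform the dose slope *b*. The fitted arm coefficient is then

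arm term = (ITT difference) − *b* × (mean sessions in the intervention arm).

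This is the intervention line read at zero sessions, minus the control mean.

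**Closed form with no true effect.** Assume mean 7 sessions, SD 3, and correlation *r* between attendance and a better (lower) outcome. Then *b* = −*r* × 14/3 and the arm term is −*b* × 7. For *r* = 0.1, 0.2 and 0.3 this gives *b* = −0.47, −0.93 and −1.40 points per session, and arm terms of +3.3, +6.5 and +9.8.

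**Simulation with baseline adjustment.** There were 4,000 trials per setting with no true effect. The baseline–outcome correlation was assumed to be 0.5. Sessions were rounded and limited to 0–10, with a realised mean of 6.76. The correlation is between attendance and the part of prognosis that baseline does not capture; a negative value means attenders do better.

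| Correlation | Dose slope | Arm term | Arm term rejected at 5% | ITT rejected at 5% |
|---|---|---|---|---|
| 0 | 0.01 | −0.05 | 4.8% | 4.8% |
| −0.1 | −0.46 | +3.1 | 20% | 5.8% |
| −0.2 | −0.91 | +6.1 | 58% | 5.3% |
| −0.3 | −1.36 | +9.2 | 90% | 5.1% |
| +0.2 | +0.89 | −6.0 | 56% | 4.6% |
| +0.3 | +1.36 | −9.2 | 91% | 4.9% |

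The algebra checks: 0.906 × 6.76 = 6.1.

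**Sensitivity at correlation −0.2.**

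- Counting the control session as dose 1 gives +5.2 (0.908 × 5.76) with 54% rejection, so the problem remains.
- Attendance set at mean 5 (SD 3), 8 (SD 2) and 9 (SD 1.5) gives +4.3, +10.3 and +16.3. Better attendance lengthens the extrapolation.

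**A true effect acting wholly through sessions.** Set −4.4/6.8 = −0.647 points per session. At correlation 0 the ITT estimate is −4.36 and the arm term is +0.05. At −0.2 the ITT estimate is −4.38, the arm term +6.1 and the dose slope −1.55 (−0.647 − 0.906).

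**Precision.** The ITT standard error is about 14 × √(1 − 0.5²) × √(2/160) = 1.36. With dose in the model, the arm term's is about 2.8.

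**Multilevel version.** Sessions attended is one value per couple. As a main effect it enters only the between-couple part, while arm-by-wave is estimated from change within couples. A null check used three waves, 160 per arm, correlations of 0.2 and 0.3, and 150 trials each. With complete data the arm-by-wave estimate was the same with and without dose. With 20% of follow-up values missing, the largest shift was about 0.1 point.

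**Instrumental alternative, same set-up.** Two-stage least squares with arm as instrument averaged 0.00 per session under no effect, with 4.6% to 5.0% rejection. With the true −0.647 it gave −0.64 to −0.65. Correlations were −0.3, −0.2, 0, 0.2 and 0.3. These data satisfy the exclusion restriction by construction.

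**The case against.** The analysis is explicitly secondary and preliminary, and the primary 12-month comparison contains no dose term. The article does not say which coefficient will be read or that either will be read causally, and such detail may sit in a document not shown. The attendance figures and correlations are assumptions. At zero correlation there is no false signal under the null, and the opposite sign is just as possible. The instrumental estimate is also no free replacement. With one binary instrument it is essentially the ITT effect divided by mean sessions (−4.36/6.76 = −0.645), so it cannot show dose-response. Its exclusion restriction is doubtful because control couples receive their own package of safety planning, referrals and alcohol education.

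Most of this stands and limits the point. What it does not remove is the printed specification: arm and dose in one rerun of the ITT models. The arm term's meaning follows from dose being constant in controls, whatever the correlation.

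A reader might infer three stronger things that the document does not support:

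- **That the trial's test of efficacy is biased.** The primary regression omits dose, and the arm-by-wave test barely moves unless a dose-by-wave term is added, which the text does not specify.
- **That couples doing better will attend more, so the bias will look like harm.** The document gives no evidence on direction.
- **That this model will set the number of sessions for scale-up.** The triangulation section mentions possible refinements but not dose.

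**Conclusion.** The point holds for the 12-month linear regression in the secondary dose analysis. There the arm coefficient is a zero-session extrapolation, not a treatment effect, and the dose coefficient is a non-randomised within-arm association. Any bias depends on attendance being related to prognosis after baseline adjustment, and can take either sign. Its size, about 0, 3, 6 or 9 IFVCS points at absolute correlations of 0, 0.1, 0.2 or 0.3, rests on assumed attendance of about 7 sessions (SD 3) and a baseline–outcome correlation of 0.5, with SD 14 and 160 per arm from the plan. Without any confounding, the arm term still misses an effect that acts through sessions. This should be corrected, but it is a moderate matter: the primary ITT result stands as planned.

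**What to change.** Replace the one sentence on dose as follows:

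1. Do not fit or interpret arm and sessions attended in the same model, do not add a dose-by-wave term to the multilevel model, and do not call the dose analysis ITT.
2. Estimate a complier-average or per-session effect by two-stage least squares, with randomised arm as the instrument for sessions and the same covariates. State the exclusion restriction and say why it is open to question given enhanced usual care in the control arm. State linearity in sessions, which also needs thought because content moves from motivational interviewing to couples therapy. Say that the estimate rescales the ITT effect and does not test dose-response.
3. Describe attendance against outcome within the intervention arm only, adjusted for baseline predictors of attendance and labelled associational.

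The cost is a wider relative interval and extra assumptions for one secondary analysis. Design, data collection and sample size do not change. If the exclusion restriction is judged untenable, the third item can stand alone.
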